#### Blinding.

The evaluators will be blinded to the data collection as each participant will be assigned a code for identification. The participants will not be blinded as they are aware of the intervention they are carrying out.

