#### Data collection and analysis.

Participants in both groups will complete self-administered online questionnaires at baseline and six weeks post-intervention.

Email reminders will be sent at each data collection time point, and if participants fail to respond, additional follow-ups will be conducted via email and, if necessary, by phone at their workplace. Upon completion, data will be securely stored, accessible only to the appointed statistician, and later exported to STATA v.16 software for analysis [50].

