#### Primary outcome.

Pain intensity: Spinal pain will be assessed using the Visual Analogue Scale (VAS) [51,52], a subjective scale ranging from 0 to 10, with 0 representing “no pain” and 10 representing “the worst possible pain.” A clinically important difference (MCID) for the VAS is defined as a 30% reduction from baseline [53], which is considered a meaningful improvement in pain intensity for musculoskeletal conditions. Therefore, any reduction of 30% or greater in VAS scores will be considered a clinically significant improvement.

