#### Secondary outcomes.

Spinal pain dysfunction: Spinal pain dysfunction will be assessed using the Spanish version of the Spine Functional Index (SFI) [54,55], a self-administered questionnaire that evaluates the impact of spinal conditions on daily activities and functional abilities. In the absence of an established MCID, we will apply the distribution-based approach, calculating the MCID as 0.5 times the standard deviation of baseline scores. This method is widely used in clinical research to estimate clinically meaningful changes based on the variability within the sample when anchor-based MCIDs are unavailable [56].

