#### Statistical analysis.

Descriptive statistics will be used to summarise the demographic and baseline characteristics of participants. Categorical variables (e.g., gender, educational level) will be compared between control and intervention group using Chi-square tests or Fisher’s exact tests, as appropriate, while continuous variables (e.g., age) will be compared using independent-samples t-tests for normally distributed variables or Mann–Whitney U tests if the data are not normally distributed. The Shapiro-Wilk test and Q-Q plots will be employed to assess normality. If the data meet normality assumptions (p > 0.05), parametric tests will be applied; otherwise, non-parametric tests will be used.

Within-group comparisons (before- vs. after-intervention) will be conducted using paired t-tests for normally distributed variables, and the Wilcoxon signed-rank test will be applied for variables not meeting normality assumptions. Changes from baseline between the intervention and control groups (before and after differences) will be evaluated using independent-samples t-tests for normally distributed data, or Mann–Whitney U tests for non-normal data. Clinically significant changes will be assessed using criteria established in previously reviewed studies.

Mixed-effects models will be employed to evaluate the effect of the intervention over time, taking into account repeated measures. A linear mixed-effects model will be applied to outcomes that are approximately normally distributed, with random intercepts included to account for within-subject variability. If an outcome clearly violates normality assumptions even after exploration or transformation, a generalized linear mixed model (GLMM) with an appropriate link function (e.g., logit for binary outcomes) may be considered. These models will adjust for potential confounders such as age, gender, educational level, spinal pathologies, job tasks, and adherence. Statistical significance will be set at a p-value of less than 0.05. Mixed-effects models are appropriate for this cluster-randomised design with repeated measures, as they account for both fixed effects and within-subject variability. Sample size was estimated assuming a moderate effect size, an ICC of 0.05, alpha = 0.05, and 80% power.

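### The claimed evaluator blinding protects no outcome assessment, because every outcome is self-reported by participants who know their allocation

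*Protocol article*

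**What the plan says.** The Blinding section of the protocol article makes two statements. The first is the claimed safeguard: "The evaluators will be blinded to the data collection as each participant will be assigned a code for identification". The second follows directly: "The participants will not be blinded as they are aware of the intervention they are carrying out".

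The quantitative-phase section on data collection and analysis then describes how outcomes are obtained: "Participants in both groups will complete self-administered online questionnaires at baseline and six weeks post-intervention". The stored data are "accessible only to the appointed statistician". The pain VAS is "a subjective scale ranging from 0 to 10", and the SFI is "a self-administered questionnaire that evaluates the impact of spinal conditions on daily activities and functional abilities". The EQ-5D-5L and the BREQ-2 are questionnaires within the same online set, and adherence comes from a diary that participants keep on the Sakai platform.

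The Statistical analysis section makes the choice of test depend on normality, judged by Shapiro-Wilk and Q-Q plots: if normality holds, "parametric tests will be applied; otherwise, non-parametric tests will be used". It also allows transformation and a possible GLMM, and it lists adherence among the covariates of the mixed models.

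**The concern.** A statement that evaluators are blinded normally means that whoever rates the outcome does not know the arm. Here the rater of each outcome is the participant, and the participant knows. The primary outcome is subjective and the comparator is a waiting list, so expectation effects are an obvious threat to the between-group comparison. A reader or risk-of-bias assessor who takes the first sentence of the Blinding section at face value could credit the trial with blinded outcome assessment that its design cannot provide. The Limitations section discusses volunteer motivation, generalisability and the lack of pain classification, but not unblinded self-report.

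A second, smaller matter is the analysis stage, where masking is feasible and would have some value. The article describes coding of participants but does not say whether the person choosing the models can see the arm.

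**Working it through.** No figure in the plan bears on this point, so the check is a reading of who produces each measurement and what the code conceals.

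**Step 1: who rates each outcome.**

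| Outcome | Section | Produced by | Rater blinded? |
|---|---|---|---|
| Pain, VAS | Primary outcome | Participant (subjective scale) | No |
| Spinal function, SFI | Secondary outcomes | Participant (self-administered) | No |
| EQ-5D-5L | Quality of life | Participant | No |
| BREQ-2 | Exercise motivation | Participant (online questionnaire) | No |
| Adherence | Adherence to the program | Participant (self-kept diary) | No |

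Unblinded self-report: 5 of 5. Rated by an evaluator: 0 of 5. The abstract counts pain, dysfunction and adherence as primary, whereas the body counts pain alone. On either version every primary outcome is unblinded self-report.

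**Step 2: what the code conceals.** An identification code replaces a name. It does not remove the arm. Under the Randomisation section whole campuses are allocated, so anyone who sees a record's campus and knows that campus's allocation knows the arm. The wording of the claim also refers to data collection and does not mention allocation.

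**Step 3: what remains open at analysis.** Shapiro-Wilk with its p > 0.05 threshold is a rule and leaves no discretion. Three elements do leave some: the judgement on Q-Q plots, whether to transform, and whether to move to a GLMM. All three are settled after the data are seen. The article neither states nor denies that the statistician is masked while settling them.

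**Step 4: whether the planned model is compatible with masking.** The mixed models are to adjust for adherence. The diary sits on the platform and records active breaks. Under the quantitative-phase Design section, controls gain access only after completing the six-week questionnaires. Up to that point only the intervention arm can have diary data, so a populated adherence variable identifies the arm. Relabelling the arms would therefore not mask an analyst whose primary VAS model contains adherence.

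**The case against.** The strongest case on the other side has four parts.

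- **The open-label nature is disclosed.** The sentence after the claim says participants are unblinded, and the next section says the questionnaires are self-administered. A careful reader can work out the position. This stands and limits the harm. It does not make the first sentence correct, because the article never draws the conclusion that outcome assessment is open-label.
- **The term evaluators is undefined.** It could mean whoever processes or analyses coded records, in which case the sentence is an attempt at analyst masking. That reading is possible. Even so, the stated means is a code that hides identity rather than arm, so the sentence needs rewriting on either reading.
- **The article does not say that the statistician is unmasked.** A reader might infer from the silence that the analysis will be run with arm labels visible. The document does not support that inference: statistician-only access to coded data is compatible with masking, and a fuller protocol or analysis plan may settle the matter. Nor is the statistician the only role that could be masked, since staff who chase non-responders by email or phone might be masked too. The statistician's exclusive access applies to the stored questionnaire data; the research team also reviews adherence weekly.
- **Participants cannot be blinded to active breaks against a waiting list, and correcting the text changes no estimate.** Both are true. The point concerns an accurate description of the safeguard and a cheap gain at the analysis stage, not a demand for participant blinding.

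**Conclusion.** The point holds in this form: the evaluator blinding described in the article protects none of the five outcome assessments, because participants who know their allocation report all of them and a participant code does not hide the arm. It would go too far to say that the statistician is unmasked; what can be said is that masking is not stated while some modelling choices stay open until the data are seen.

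The affected share is all five outcomes, including the primary one. The size of the bias, whether from expectation or from analysis choices, cannot be derived from the document. The conclusion rests on two assumptions: that the instruments are used as described, with no separate assessor-rated measure, and that controls have no diary to fill in before they gain platform access. The correction is worth making before results are reported, but it does not alter the sample size or the data collected.

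**What to change.** 1. **Blinding section.** Replace the sentence on evaluators with a statement that all outcomes are self-reported by unblinded participants, so that outcome assessment is open-label.
2. **Limitations section.** Add that the subjective primary outcome is self-reported by participants who know their allocation and is compared with a waiting list, so expectation effects cannot be excluded.
3. **Give the coding a masking function.** Supply the analysis file with arms relabelled A and B and campuses relabelled 1 to 6 until the primary VAS model and data set are locked, and say so in the text.
4. **Take adherence out of the primary VAS model.** Item 3 depends on this, because the variable reveals the arm. Release the diary data after the lock and use them in secondary analyses. The covariate list in the Statistical analysis section must be changed to match.

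The cost is one rewritten paragraph, one added limitation, a small relabelling task for someone outside the analysis, a short delay before the adherence analyses, and a less favourable blinding statement. Recruitment, instruments and intervention are unaffected.

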#### Data collection and analysis.

Participants in both groups will complete self-administered online questionnaires at baseline and six weeks post-intervention.

Email reminders will be sent at each data collection time point, and if participants fail to respond, additional follow-ups will be conducted via email and, if necessary, by phone at their workplace. Upon completion, data will be securely stored, accessible only to the appointed statistician, and later exported to STATA v.16 software for analysis [50].

#### Primary outcome.

Pain intensity: Spinal pain will be assessed using the Visual Analogue Scale (VAS) [51,52], a subjective scale ranging from 0 to 10, with 0 representing “no pain” and 10 representing “the worst possible pain.” A clinically important difference (MCID) for the VAS is defined as a 30% reduction from baseline [53], which is considered a meaningful improvement in pain intensity for musculoskeletal conditions. Therefore, any reduction of 30% or greater in VAS scores will be considered a clinically significant improvement.

#### Secondary outcomes.

Spinal pain dysfunction: Spinal pain dysfunction will be assessed using the Spanish version of the Spine Functional Index (SFI) [54,55], a self-administered questionnaire that evaluates the impact of spinal conditions on daily activities and functional abilities. In the absence of an established MCID, we will apply the distribution-based approach, calculating the MCID as 0.5 times the standard deviation of baseline scores. This method is widely used in clinical research to estimate clinically meaningful changes based on the variability within the sample when anchor-based MCIDs are unavailable [56].

#### Quality of life.

Quality of life will be evaluated using the Spanish version of the EQ-5D-5L questionnaire [57,58], which covers five dimensions: mobility, self-care, daily activities, pain/discomfort, and anxiety/depression. Participants respond to the EQ-5D-5L questionnaire by indicating their level of impairment or difficulty in each dimension on a five-level scale, ranging from no problems to extreme problems. The responses provide quantifiable data that can be analysed to assess overall health status and quality of life, guiding healthcare interventions and treatment planning. Since there is no established MCID for the EQ-5D-5L in this population, we will also apply the distribution-based approach, using 0.5 times the standard deviation of baseline scores to estimate the MCID [56].

#### Exercise motivation.

Exercise motivation will be assessed using the Spanish version of the Behavioural Regulation in Exercise Questionnaire-2 (BREQ-2) [59–61], which evaluates five distinct types of motivation: intrinsic motivation, identified regulation, introjected regulation, external regulation, and amotivation. The BREQ-2 has been validated for use in individuals with chronic musculoskeletal pain, making it suitable for assessing exercise motivation in this population. The same distribution-based approach used for other measures lacking anchor-based MCIDs (i.e., 0.5 times the standard deviation of baseline scores) will be employed to determine clinically meaningful changes [56]. Significant increases in intrinsic motivation (exercising for enjoyment) and identified regulation (exercising because it is personally important) will be considered meaningful for predicting better adherence to the exercise intervention [28].

#### Adherence to the program.

Therapeutic adherence will be assessed using a self-administered diary available on the Sakai platform, where participants will record the active breaks they performed at the end of each workday. To promote adherence, reminder emails will be sent at the start and end of each week to prompt participants to complete their diary entries. Adherence data will be reviewed weekly by the research team to monitor participant engagement. If adherence remains unreported at the end of the week, a personalised follow-up email from the supervising physiotherapist will be sent at the start of the following week.

This diary serves as a tool to monitor and evaluate participants’ compliance with the intervention, providing valuable insights into their engagement with the prescribed active break regimen. The 80% adherence rate is considered satisfactory in pain management interventions [62,63].

#### Statistical analysis.

Descriptive statistics will be used to summarise the demographic and baseline characteristics of participants. Categorical variables (e.g., gender, educational level) will be compared between control and intervention group using Chi-square tests or Fisher’s exact tests, as appropriate, while continuous variables (e.g., age) will be compared using independent-samples t-tests for normally distributed variables or Mann–Whitney U tests if the data are not normally distributed. The Shapiro-Wilk test and Q-Q plots will be employed to assess normality. If the data meet normality assumptions (p > 0.05), parametric tests will be applied; otherwise, non-parametric tests will be used.

Within-group comparisons (before- vs. after-intervention) will be conducted using paired t-tests for normally distributed variables, and the Wilcoxon signed-rank test will be applied for variables not meeting normality assumptions. Changes from baseline between the intervention and control groups (before and after differences) will be evaluated using independent-samples t-tests for normally distributed data, or Mann–Whitney U tests for non-normal data. Clinically significant changes will be assessed using criteria established in previously reviewed studies.

Mixed-effects models will be employed to evaluate the effect of the intervention over time, taking into account repeated measures. A linear mixed-effects model will be applied to outcomes that are approximately normally distributed, with random intercepts included to account for within-subject variability. If an outcome clearly violates normality assumptions even after exploration or transformation, a generalized linear mixed model (GLMM) with an appropriate link function (e.g., logit for binary outcomes) may be considered. These models will adjust for potential confounders such as age, gender, educational level, spinal pathologies, job tasks, and adherence. Statistical significance will be set at a p-value of less than 0.05. Mixed-effects models are appropriate for this cluster-randomised design with repeated measures, as they account for both fixed effects and within-subject variability. Sample size was estimated assuming a moderate effect size, an ICC of 0.05, alpha = 0.05, and 80% power.

An intention-to-treat analysis will be conducted, ensuring that all participants are analysed in their originally assigned groups. Missing data will be addressed using complete-case analysis, assuming data are missing at random. Sensitivity analyses will be considered to assess the potential impact of missingness on the results. All statistical analyses will be performed using STATA v.16 software [50].

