**Methods:**

This study follows a sequential exploratory mixed-methods design. The qualitative phase will use semi-structured interviews with office workers to explore their experiences with spinal pain, active breaks, and perceived barriers to implementation. These findings will inform the development of a six-week web-based therapeutic exercise intervention, which will be evaluated through a two-arm cluster randomised controlled trial. The trial will compare an intervention group performing structured active breaks during work hours with a control group maintaining their usual routine. Primary outcomes include pain intensity (Visual Analogue Scale), spinal dysfunction (Spine Functional Index), and adherence to the program. Secondary outcomes include quality of life (EQ-5D-5L) and exercise motivation (Behavioural Regulation in Exercise Questionnaire-2). Statistical analyses will compare within- and between-group differences to assess the intervention’s effectiveness.

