#### Sample size calculation.

The GRANMO calculator has been used to obtain the sample size. The study by Kenneth et al [48], has been taken for reference with a minimum significant difference in pain intensity of 1.5 and a standard deviation of 1.5, considering an alpha risk of 0.05 and a statistical power of 95% to reject the null hypothesis, the minimum number of participants per group necessary will be 33 accounting for an expected 20% dropout rate.

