#### Randomisation: type and sequence generation.

Participants in the study will be assigned to either the Intervention Group or the Control Group through cluster randomisation. The six campuses of the University will be randomised into either group to prevent contamination between groups. A 1:1 ratio will be maintained to ensure an equal distribution of campuses between the experimental and control clusters. The randomisation will be conducted using Study Randomizer, a web-based service, to ensure unbiased allocation [49].

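### No stated between-group analysis of pain gains the precision of adjusting for baseline VAS, and the abstract counts within-arm changes as evidence of effectiveness

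*Protocol article*

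**What the plan says.** The Statistical analysis section of the protocol article applies three procedures to each outcome, including pain on the VAS.

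- **Within arms:** paired t-tests, or Wilcoxon signed-rank tests where normality fails.
- **Between arms, on change:** "Changes from baseline between the intervention and control groups (before and after differences) will be evaluated using independent-samples t-tests for normally distributed data". Where normality fails, a Mann–Whitney test takes its place. The switch is a rule: "If the data meet normality assumptions (p > 0.05), parametric tests will be applied; otherwise, non-parametric tests will be used". Normality is assessed by Shapiro–Wilk and Q-Q plots.
- **Mixed model:** a linear mixed model with random intercepts for within-subject variability. The adjustment variables named are age, gender, education, spinal pathologies, job tasks and adherence, given as examples. Baseline VAS is not among them.

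The same section specifies complete-case analysis. The quantitative-phase section on data collection gives two measurement times, baseline and six weeks. The abstract's sentence on how effectiveness will be judged begins: "Statistical analyses will compare within- and between-group differences to assess".

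**The concern.** Baseline VAS is measured on everyone and will normally be the strongest predictor of week-6 VAS. A comparison of raw changes subtracts it with a coefficient fixed at 1. A model that estimates the coefficient is more precise whenever the baseline-to-follow-up correlation is below 1. In a trial of this size the loss is worth avoiding.

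The mixed model seems to answer this, because it uses the baseline measurement. It uses it as an outcome, however, and the working below shows that in this design it returns the change-score result.

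The within-arm tests are a different matter. A before–after change in one arm mixes any treatment effect with natural course, regression to the mean and expectation. Participants are unblinded and controls are on a waiting list. If such a test counts towards effectiveness, a trial with no treatment effect can look positive.

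**Working it through.** **Inputs from the protocol.** The sample size calculation gives the target as "minimum significant difference in pain intensity of 1.5 and a standard deviation of 1.5". It sets alpha at 0.05 and power at 95%, and arrives at 33 per arm after allowing for 20% dropout. Randomisation: six campuses, 1:1.

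**Assumed, not in the protocol.** The baseline-to-week-6 correlation ρ (range 0.3 to 0.8) and the size of any improvement common to both arms.

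**1. The plan's own figure.** n per arm = 2(1.960 + 1.645)² × (1.5/1.5)² = 25.99, so 26. With 20% dropout, 26/0.8 = 32.5, so 33. The stated number reproduces for a two-sided test of independent participants. The 26 completers per arm are used below.

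**2. Change score against baseline adjustment.** With equal variance σ² at both times:

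- variance of the change = 2σ²(1 − ρ)
- residual variance after baseline adjustment = σ²(1 − ρ²)
- ratio = (1 + ρ)/2

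The standard error of the difference is the corresponding SD × √(2/26). The protocol does not say whether 1.5 is the SD of a score or of a change, so both readings are shown.

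| ρ | Variance ratio | SE, change → adjusted (1.5 = SD of score) | SE, change → adjusted (1.5 = SD of change) |
|---|---|---|---|
| 0.3 | 0.65 | 0.492 → 0.397 | 0.416 → 0.335 |
| 0.5 | 0.75 | 0.416 → 0.360 | 0.416 → 0.360 |
| 0.7 | 0.85 | 0.322 → 0.297 | 0.416 → 0.384 |
| 0.8 | 0.90 | 0.263 → 0.250 | 0.416 → 0.395 |

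In simulation at ρ = 0.5, with SD 1.5 at each time and a true difference of 0.9 points, power was 56% for the change-score test chosen by the normality rule and 67% for the baseline-adjusted analysis. All figures in this step treat participants as independent.

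**3. Does the planned mixed model recover the gain?** With two times, complete pairs and a subject random intercept, the group-by-time term is estimated from within-subject differences, that is, from the change scores. In one simulated data set (26 per arm, ρ = 0.5) the model and the change-score t-test gave the same estimate, −1.057, and the same t, −2.991, with SE 0.353. Adding age as a main effect left the estimate and SE unchanged. The baseline-adjusted analysis of the same data had SE 0.292. Only a version that constrains the arms to equal baseline means would match it, and the protocol does not describe one.

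**4. Within-arm test with no treatment effect.** For a paired t-test with n = 26 and SD of change 1.5, the noncentrality is shift/1.5 × √26 and the two-sided critical value is 2.06.

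| Improvement common to both arms | Noncentrality | Chance of p < 0.05 in a given arm |
|---|---|---|
| 0.5 points | 1.70 | 37% |
| 0.75 points | 2.55 | 69% |

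In simulation with a common improvement of 0.7 points and no treatment effect, the intervention arm alone was significant in about 23% of trials.

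**5. The normality switch.** In 4,000 simulated null trials without clustering, the selected test rejected in 4.7% (normal data) and 5.2% (skewed data). This is essentially nominal.

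**6. Campus.** With ICC 0.05 and campus ignored, the change-score tests and the baseline-adjusted analysis each rejected in about 9% of null trials. Baseline adjustment alone therefore does not make the inference valid; campus must be in the model.

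**The case against.** The case against is substantial, and several parts of it stand.

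- **The covariate list is open.** The named variables are examples, and an analysis plan that is not shown may add baseline VAS. It cannot be said that baseline VAS is excluded. What the protocol does state, however, is an unadjusted change-score comparison and a subject-random-intercept model, and those are the less precise choices.
- **A reader might infer that no analysis leads.** The section does describe the mixed model as the one that evaluates the intervention effect and calls it suited to the design. That is a fair pointer. It does not help precision, because of step 3, which supposes that the effect is read from the group-by-time term.
- **A reader might infer that the normality pre-test inflates type I error, or that it is wrongly applied to raw data.** The first is not borne out by step 5. The second is not stated: for the between-group comparison the tested data may well be the changes. The remaining drawback is modest. A Mann–Whitney result gives no mean difference to set against the 1.5-point target, although the mixed model can supply one.
- **A reader might infer that chance baseline imbalance across six campuses biases the change-score test.** Under randomisation that comparison is unbiased; it is only less efficient. No harm from regression to the mean in the between-group test has been shown.
- **A reader might infer that the conclusion will be drawn from a within-arm p-value.** The abstract names within- and between-group differences together, and the Statistical analysis section does not make the within-arm tests decisive. The objection is to giving them any role in judging effectiveness.

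**Conclusion.** The concern holds as a matter of efficiency and interpretation. The analyses written down for the between-group effect forgo a variance reduction of about 35% to 10% for ρ from 0.3 to 0.8. At ρ = 0.5 the SE falls from 0.416 to 0.360. These sizes rest on an assumed correlation, equal variances at the two times, 26 completers per arm and no clustering, so they are not the precision this trial will have. With 26/3 completers per campus and the protocol's ICC of 0.05, the design effect for a single measurement is 1 + (26/3 − 1) × 0.05 = 1.38.

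The within-arm tests cannot support a claim of effectiveness. The 37% and 69% figures depend on the assumed common improvement, but some shared improvement is plausible with unblinded participants and a waiting-list control. The change-score test is valid in principle once clustering is handled. This is a worthwhile improvement at almost no cost, not an error that invalidates the trial.

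**What to change.** - **Primary analysis:** week-6 VAS in a linear mixed model with arm and baseline VAS as fixed effects and campus as a random effect, with a small-sample correction for six clusters such as Kenward–Roger. A longitudinal model with baseline means constrained equal between arms, and campus handled in the same way, is an acceptable equivalent.
- **Reporting:** give the adjusted mean difference and its 95% confidence interval whatever the normality test shows. Check residuals, and keep rank tests as a sensitivity analysis.
- **Within-arm changes:** report them descriptively, without p-values, and delete the reference to within-group differences from the abstract's effectiveness sentence.
- **Covariates:** adherence arises after randomisation and should not be carried into this model.

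The cost is a revision of the analysis wording. Baseline VAS and campus are already recorded, and no extra data or participants are needed for this change.
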